### Data management and confidentiality

Data generation, transmission, storage, and analysis follow Swiss legal requirements for data protection. Personal data are considered confidential and disclosure to third parties is prohibited. The anonymity of participants is guaranteed by utilizing unique subject identification code numbers that are consecutively generated by a computerized list. Personal data and the allocation list are locked separately from anonymized baseline variables and outcome data. Unblinding of outcome assessors towards allocation is permissible upon completion of T_4_. Data of all outcomes as well as case report forms will be archived (1) in folders that are stored in locked study closets, and (2) electronically on personalized password-secured desktop computers. Backups are automatically performed every hour. Access is provided to authorized study personnel, the Clinical Trial Board of the Kliniken Valens hospital group, and the local Ethics committee at all times for purposes of trial-related monitoring, audits, review, and regulatory inspections.

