### Aim, study design, and setting

CYPRO is a parallel-group, single-center, and single-blind randomized controlled superiority trial that is performed at the Valens rehabilitation clinic, Switzerland.

The aims of CYPRO are described as the following:

1. Primary aim: To investigate the effects of HIIT compared to MCT on cardiorespiratory fitness, as indicated by peak oxygen consumption (V̇O_2peak_).

2. Secondary aims: To investigate the effects of HIIT compared to MCT on peak power output (PPO), walking capacity, cognitive performance, HRQoL, fatigue, anxiety and depressive symptoms, and blood-derived biomarkers related to MS pathophysiology. Additionally, CYPRO aims to investigate the acute effects of a single HIIT session compared to a single MCT session on changes in blood-derived biomarkers.

HIIT represents the experimental condition that is hypothesized to be superior to the standard treatment MCT as an active comparator. The study design and flow of participants are illustrated in Fig. 1.

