### Recruitment and randomization procedure

All pwMS entering the Valens rehabilitation clinic for an inpatient stay are screened for study eligibility. Eligibility screening is performed as a two-step process. In the first step, PPMS diagnosis and EDSS score are checked in advance of clinic admission. In the second step, all other eligibility criteria are checked by in-person consultation on the day of clinic admission. Sixty-one pwPPMS will be recruited. As the sex ratio in pwPPMS is 1:1, we pursue recruiting an equal number of female and male pwPPMS [14]. The number of screened pwMS in total and per screening step, as well as reasons for ineligibility are documented.

Stratified randomization to either HIIT or MCT (1:1) is performed by a group of blinded investigators not involved in CYPRO. Allocation sequence generation is performed using random-sized (block size 4–6) permuted block randomization with Randomization-In-Treatment-Arms (RITA) software (Version 1.51, Evident, Lübeck, Germany). To ensure allocation concealment, the blinded investigators are called for assignment each time a participant presents for inclusion [24]. CYPRO study personnel that performs enrolment, obtains consent, and assigns participants has no access to details on the allocation sequence and blocking. Strata include relative V̇O_2peak_ (mL · min^-1^ · kg-^-1^) at baseline, sex, age, and EDSS score.

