### Exercise protocols

Within their three-week inpatient stay at the Valens rehabilitation clinic, participants perform two to three weekly HIIT or MCT sessions on bicycle ergometers (Cybex 750 C, Cybex International Inc., Massachusetts, USA) in addition to standard rehabilitative care. Standard rehabilitative care comprises endurance and strength training (30-45 minutes, three to five times per week), physiotherapy to improve balance and/or walking ability (30 minutes, daily) as well as occupational therapy focused on fatigue management and activities of daily living (30 minutes, two to three times per week). Exercise volume of HIIT and MCT protocols have been matched in Units of Exercise. Units of Exercise are calculated as [intensity (percentage of peak heart rate (%HR_peak_)) x session duration (minutes) x frequency (number of sessions per week) x number of weeks] [25]. %HR_peak_ is derived from HR_peak_ achieved during CPET at baseline. During sessions, HR is continuously recorded by HR sensors (H10 HR sensor, POLAR, Kempele, Finland) attached to chest belts, and connected to wristwatches (M430 sports watch, POLAR, Kempele, Finland). Both, HIIT and MCT are conducted under the supervision of trained exercise scientists and physiotherapists, either individually or in small groups of up to three participants. Therapists are instructed to monitor the HR, and to adjust pedaling resistance in case of deviations from the target intensity. If participants are unable to follow the prescribed protocols (e.g., due to pronounced ankle flexor spasticity), dose modifications (i.e., decreasing revolutions per minute (rpm) or interval duration, increasing break duration) are permissible. Any dose modification is documented in a case report form. Blinding of therapists and participants towards group allocation is not feasible due to the study design.

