### Outcomes

V̇O_2peak_, PPO, walking capacity, cognitive performance, HRQoL, fatigue, and anxiety and depressive symptoms are assessed by allocation-blinded outcome assessors at study entry (baseline, T_0_) and discharge after three weeks (T_4_), at least 48 hours after the last HIIT or MCT session. Venous blood samples are taken before (T_1_), immediately after (T_2_), and two hours after (T_3_) the first HIIT or MCT session, and at T_4_.

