**Fig. 2 Fig2:**
[figure not shown]
SPIRIT 2013 diagram Abbreviations: HIIT = high-intensity interval training; MCT = moderate-intensity continuous training; MoCA = Montreal Cognitive Assessment; CPET = cardiopulmonary exercise testing; PPO = peak power output in watts during CPET; BICAMS-M = German modification of the Brief International Cognitive Assessment for Multiple Sclerosis; 6-MWT = six-minute walk test; MSIS-29 = Multiple Sclerosis Impact Scale; FSMC = Fatigue Scale for Motor and Cognitive Functions; HADS = Hospital Anxiety and Depression Scale. T_− 1_= day of admission; T_0_ = day of study entry (baseline assessment prior group allocation); T_1_ = immediately before the first exercise session; T_2_ = immediately after the first exercise session; T_3_ = two hours after the first exercise session; T_4_ = at discharge after three weeks, at least 48 h after the last exercise session

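### The unblinding rule is tied to T4, a participant-level visit, so assessors may learn completed participants' allocations while recruitment continues, which weakens the blinding of later assessments

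*Protocol article*

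**What the plan says.** - **Unblinding rule** (Data management and confidentiality): "Unblinding of outcome assessors towards allocation is permissible upon completion of T_4". The sentence names no trial-level condition such as last participant, end of data collection or database lock.
- **Meaning of T4** (legend of Fig. 2): "T_4_ = at discharge after three weeks, at least 48 h after the last exercise session". The Outcomes section uses T4 in the same participant-level sense.
- **Who is blinded** (Outcomes): performance tests and questionnaires "are assessed by allocation-blinded outcome assessors at study entry" and again at discharge.
- **Who is not blinded** (Exercise protocols): "Blinding of therapists and participants towards group allocation is not feasible due to the study design".
- **Allocation** (Recruitment and randomization procedure): 1:1, stratified, with "random-sized (block size 4–6) permuted block randomization". The four stratification factors are baseline relative V̇O2peak, sex, age and EDSS score; the number of levels is not given. Staff who enrol, take consent and assign are denied the sequence and the blocking. Outcome assessors are not mentioned there.
- **Progress** (Study status): the first participant was enrolled on 13 March 2022, 23 had been recruited by March 2023, and recruitment was continuing.

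**The concern.** This is a rule that the article states, not a detail left to a fuller document. The trial is single-centre with staggered entry, and its outcome data are protected by assessor blinding alone. A rule triggered by each discharge visit lets the assessing staff build up knowledge of allocations as the trial proceeds. Two routes to bias follow.

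1. **Prediction.** In small balanced blocks, past allocations carry information about the next one.
2. **Linkage.** Assessors can connect results that they measured themselves with the arm before they test later participants, in a trial that openly expects HIIT to win.

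The exposed measurements are the exercise test, which ends when the participant feels exhausted and yields the primary outcome, and the BVMT-R, where the assessor rates each figure from 0 to 2. The SDMT is also recorded by the assessor, but it is a count of correct answers and leaves less room for judgement.

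**Working it through.** The article gives no figure on this point to reproduce. The check is a reading of the text, followed by a size estimate.

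**Step 1: does the wording allow unblinding during the trial?** The rule takes effect when T4 is complete. T4 is defined by an individual's discharge and last exercise session. No section adds a later condition. Where the authors mean a trial-level milestone they name one: in the Compliance section, adherence is derived from the heart-rate recordings only once data collection has ended. On the text, the answer is yes.

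**Step 2: how many allocations could be known at a typical T4?**
- Recruitment pace: 23 / 12 months = 1.92 per month.
- Participants in the trial at one time, with a 21-day stay: 1.92 × 21/30.4 = 1.3.
- Time to recruit 61 at that pace: 61 / 1.92 = about 32 months.
- Still to be recruited in March 2023: 61 − 23 = 38.

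At most T4 visits, therefore, nearly all earlier participants have completed T4 and their arms may already be known.

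**Step 3: what does that knowledge yield?** Stratified permuted blocks were simulated.
- From the article: N = 61, 1:1 allocation, block sizes in the range 4–6.
- Assumed: sizes 4 and 6 equally likely; 1 to 16 equally likely strata (16 = 2⁴, four factors at two levels each).
- Guessing rule: choose the arm that is behind in the participant's stratum; toss a coin if the arms are level.
- 3,000 replicates.

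| Strata (assumed) | Correct guess, all earlier allocations in stratum known | Correct guess, latest participant in stratum still blinded |
|---|---|---|
| 1 | 68.9% | 58.8% |
| 2 | 68.6% | 58.9% |
| 4 | 68.0% | 58.5% |
| 8 | 66.4% | 57.9% |
| 16 | 63.6% | 56.1% |

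A repeat with 8,000 replicates and another seed agreed to within about half a percentage point (for 16 strata, 63.5% and 56.0%). The ranges are thus about 63–69% and 56–59%. If assessors know no past allocations, the rate is 50%.

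**Step 4: can this be turned into bias in V̇O2peak?** No. The article gives nothing on how far an assessor's expectation moves the test result, so no figure is offered.

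**The case against.** **The sentence may mean the end of all T4 assessments.** It stands beside the locking of the allocation list and does not say that it applies participant by participant. That may be what the authors intended. But T4 is defined only for the individual, and the text as it stands permits the earlier unblinding, so the ambiguity itself needs removing.

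**No participant is assessed by someone who has been told that person's arm.** This is correct. A reader might infer that the 38 participants still to be recruited would be tested by unblinded assessors. The article does not support that: baseline precedes allocation, T4 must be done by blinded assessors, and the rule releases an arm only after that person's own T4. What leaks is indirect information from other participants.

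**The guess rate is easily overstated.** For a single known, fixed block size, the expected rate for a block of 2k is [k + 2^(2k−1)/C(2k,k) − 0.5]/(2k). This gives (2 + 8/6 − 0.5)/4 = 70.8% for k = 2 and (3 + 32/20 − 0.5)/6 = 68.3% for k = 3. These are not this trial's figures, because block sizes vary at random and four factors split the sample; with 16 strata there are about 61/16 = 3.8 participants in each. Even the simulated rates suppose an assessor who tracks strata and past allocations, and nothing in the article says that assessors do so.

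**Training together reveals little.** Sessions run "either individually or in small groups of up to three participants", so one might infer that one disclosed arm exposes co-trainees. The article does not say that groups are single-arm, and with about 1.3 participants in the trial at once, overlap is limited. This is a minor route.

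**The outcomes are partly protected.** V̇O2peak is measured breath by breath and is subject to attainment criteria for respiratory ratio, heart rate and perceived exertion. Encouragement is barred in the six-minute walk test, the questionnaires are self-reported, and the biomarkers are laboratory assays. This stands and limits the harm. It does not remove it for the exercise test, for which no such bar on encouragement is stated, or for the BVMT-R.

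**Conclusion.** The point holds in limited form. As written, the rule lets outcome assessors learn completed participants' arms while others are still to be tested, and nothing elsewhere in the article corrects it. Assessor blinding is weakened, not removed. The chance of guessing a later participant's arm rises from 50% to about 63–69%, or about 56–59% if the stratum's latest participant is still blinded. Both ranges assume 1 to 16 equally likely strata, blocks of 4 or 6 with equal probability, and an assessor who knows and uses the past allocations. Linkage of earlier results to arm is a second route and cannot be quantified. It would go too far to conclude that the primary result will be biased, or by how much: the article gives no basis for either, and the V̇O2peak criteria work against it.

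**What to change.** Amend the sentence in the data management section so that outcome assessors may be unblinded only after the last participant's T4 assessment is complete, except where safety requires it. State as well that allocations and any by-arm results of the interim analysis (planned at 15 HIIT and 16 MCT participants) are withheld from assessors until then. Waiting for database lock would be stricter, but it is not needed to close the routes described here.

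The cost is a one-sentence amendment and a briefing of the assessing staff. It adds no visits, staff or data collection, and the article gives no reason why assessors need the allocations sooner. With 38 of 61 participants still to be recruited in March 2023, the change would have covered the larger part of the trial from that date. Any assessor who has already been told allocations should be recorded, so that the trial report can describe the blinding accurately.

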### Statistical analysis

Statistical analyses are performed according to the intention-to-treat principle. Descriptive statistics will be reported as arithmetic mean (*M*) and standard deviation (*SD*) for continuous data, and as absolute number and percentage (*%*) for categorical data for the total sample, and separated by group. Outcome data will be checked for normality (Shapiro-Wilk test) in advance. If necessary, analyses will be adjusted accordingly. If missing values are < 5%, ANCOVA will be performed to detect time*group interaction effects and main effects of time. In that case, effect sizes will be calculated as partial eta squared (*pη*^*2*^). Otherwise, a baseline-adjusted Mixed Model for Repeated Measures (MMRM) approach, with group, time and the group × time interaction as fixed effects (type III sums of squares, CS covariance structure over time) is used to assess between-group differences over time. Bonferroni-corrected pairwise comparisons of estimated marginal means of the group × time interaction are computed. Effect sizes will be reported as Cohen’s *d* with 95% confidence interval (*CI*). For all analyses, the level of significance is set at *p* = .05. Within-group differences and between-group differences are depicted as point estimates and measures of variability for all outcomes. Bivariate correlation analyses will be conducted to determine potential associations between changes in V̇O_peak_, PPO, walking capacity, cognitive performance, HRQoL, fatigue, anxiety and depressive symptoms, and blood-based biomarkers using Pearson’s *r*. All statistical analyses will be conducted with IBM SPSS Statistics for Windows (Version 29.0., IBM Corp., Armonk, New York, USA). Besides the final analysis, one interim analysis will be performed upon collection of 50% of participant data (HIIT: *n* = 15, MCT: *n* = 16).

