### Sample size calculation

Sample size calculation for the estimated effect of HIIT or MCT on the primary outcome V̇O_2peak_ was performed using G*Power software (Version 3.1.9.7, Heinrich Heine Universität, Düsseldorf, Germany) [20]. Estimating a drop-out of 15%, a total of 61 participants (HIIT: *n*= 30, MCT: *n*= 31) was found to be sufficient to identify a small to moderate effect (*ES* ≥ 0.15) in ANOVA analysis on 2 group (HIIT vs. MCT) * 2 time (T_0_ vs. T_4_) interaction. Power was set at 80% and alpha at 0.05. Correlation among repeated measures was set at 0.6.

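### For outcomes measured only at T0 and T4, including the primary VO2peak, the stated model is incoherent: T0 is needed both as covariate and as response, and the primary contrast is not fixed

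*Protocol article*

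**What the plan says.** The Outcomes section of the protocol article has VO2peak, power output, walking, cognition and the questionnaires assessed at T0 and at T4 only. Blood is drawn at T1, T2, T3 and T4.

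The Sample size calculation rests on an interaction test, "in ANOVA analysis on 2 group (HIIT vs. MCT) * 2 time", with T0 and T4 as the two time levels.

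The Statistical analysis section gives one set of rules for all outcomes:
- With missing values below 5%: "ANCOVA will be performed to detect time*group interaction effects and main effects of time".
- Otherwise: "Otherwise, a baseline-adjusted Mixed Model for Repeated Measures (MMRM) approach, with group, time and the group" × time interaction as fixed effects, with a CS covariance structure over time.
- Afterwards: "Bonferroni-corrected pairwise comparisons of estimated marginal means of the group" × time interaction. The family of comparisons is not named.

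**The concern.** With one post-baseline value there are two coherent ways to use T0, and the text asks for both at once.

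- If T0 is the covariate, the response is T4 alone. Time then has one level, so there is no time effect, no group × time term and no covariance over time.
- If T0 is a response, so that time has two levels, adjusting for T0 regresses the T0 row on itself.

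The ANCOVA branch fails in the same way, because it promises a time × group interaction and a main effect of time. No other model is given for the primary outcome.

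What is at stake is the primary inference of a superiority trial. Depending on how the analyst resolves the conflict, the result is an interaction test that gains nothing from adjustment, a T4 contrast with too small a standard error, or a sound ANCOVA. The text does not say which.

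**Working it through.** **Inputs.** From the Sample size calculation: "Power was set at 80% and alpha at 0.05"; "Correlation among repeated measures was set at 0.6"; effect size 0.15; "Estimating a drop-out of 15%, a total of 61 participants" (30 + 31). Two assumptions are mine: the effect size is Cohen's f, as G*Power uses it, and the SD is 1 at both times. In a 2 × 2 interaction, f = 0.15 is then a difference in change of 4 × 0.15 = 0.6 SD. Completers: 61 × 0.85 = 51.9, about 52.

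**The plan's own figure.** For the interaction, λ = f² × N × 2/(1 − ρ), on 1 and N − 2 degrees of freedom.
- N = 52: λ = 0.0225 × 52 × 2/0.4 = 5.85, power 66%.
- N = 61: λ = 6.86, power 73%.
- 80% power needs 72 completers, or 72/0.85 = 85 randomised.

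The stated 61 therefore does not reproduce from the stated inputs. That is a separate matter; here the calculation only sets the reference power.

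**T0 as response and covariate, complete data.** Write S = (T0 + T4)/√2 and D = (T4 − T0)/√2. The covariate is constant within a person, so it enters S and cancels from D.

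*Interaction.* This test uses D only, so it is the change-score t test. In simulation (30 + 31, 6,000 runs) the two statistics agreed exactly. Type I error was 5.0% and power at 0.6 SD was 73%, the same with or without the covariate.

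*T4 arm contrast.*
- Fitted slope on T0: b = (1 + ρ)/2 = 0.8.
- Residual variance at T0: (1 − 0.8)² = 0.04.
- Residual variance at T4: 1 + 0.8² − 2 × 0.8 × 0.6 = 0.68.
- CS assigns both rows the average: (0.04 + 0.68)/2 = 0.36.
- The true factor for the T4 contrast is 0.68, so the standard error is too small by √(0.68/0.36) = 1.37.
- Type I error = 2 × [1 − Φ(z/1.374)], where z is the critical value for the Bonferroni family:

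| Comparisons in the family | z | Type I error |
|---|---|---|
| 1 (arms compared within a time point) | 1.960 | 15.4% |
| 2 | 2.241 | 10.3% |
| 4 | 2.498 | 6.9% |
| 6 (all cell pairs) | 2.638 | 5.5% |

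Simulation gave 15.4% for one comparison and 10.3% for two. For correlations of 0.3 to 0.9 the family-of-one figure runs from 14.3% to 16.3%.

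**Same model, 15% of T4 missing at random.** This is the situation the mixed model is meant for. At correlation 0.6 the interaction test rejected 6.6% under the null and the T4 contrast 16.8% (11.1% with a family of two). At 0.8 the figures were 6.9% and 18.0%. The interaction is then no longer identical to the change-score test. Its simulated power of 71% at 0.6 SD is above 66%, but is obtained at an inflated error rate.

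**ANCOVA of T4 on arm and T0.** Residual variance is 1 − 0.6² = 0.64, and λ = 0.6² × N/(4 × 0.64).
- N = 52: λ = 7.31, power 75.5%.
- N = 61: power 82%.
- 80% power needs 58 completers, against 72 for the interaction test.
- Simulated type I error: 5.2% with complete data, 4.9% with 15% missing.

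**Which branch applies.** If missing values means participants without T4, below 5% means at most 3 of 61. With 15% drop-out, P(X ≤ 3) = 1.3%. Counted over T0 and T4 values together (at most 6 of 122), it is 17%. Either way the mixed model is the likely branch.

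**The case against.** The strongest reply is that the article nowhere says T0 enters twice. The analysis paragraph is generic, and a baseline-adjusted repeated-measures model is coherent for the biomarkers, which have several samples after T1. Using T0 only as covariate, or only as a constrained response, causes no inflation, and exact coding may sit in an analysis plan that is not shown. This stands in part: double use is inferred. But the article itself states the terms and the covariance structure, and each harmless reading discards part of what it states.

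A reader might infer that the trial's primary test has a 15% type I error. The documents do not support that. The figure concerns a follow-up contrast, under an inferred coding, with a Bonferroni family of one. The trial was sized on the interaction, which holds 5% with complete data and drifts to 6–7% with 15% missing.

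The power gap is a loss of efficiency. The change-score test is valid and matches the sample-size method.

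It is also consistent to expect 15% drop-out and provide a mixed model at 5% or more missing. The 5% switch and the normality check on outcome data are secondary.

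**Conclusion.** The concern holds in this form: for VO2peak and the other two-point outcomes, the model cannot be fitted coherently as written, in either branch, and the primary contrast is left open. That conclusion needs only the visit schedule and the stated model terms.

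The sizes are conditional. They assume T0 is used as both response and covariate, equal variances, a correlation of 0.6 and T4 missing at random. The T4 contrast's range of about 15% down to 5.5% is for complete data and depends on the unnamed Bonferroni family. The comparison of 66% with about 75% power further assumes that the stated effect size is Cohen's f, and 52 completers.

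**What to change.** For outcomes measured only at T0 and T4, state one primary model that applies whatever the amount of missing data. Either of these will do:

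1. T4 value on arm and T0 value, plus the stratification factors, with no time terms.
2. A constrained longitudinal model with T0 and T4 as responses, a common baseline mean, an unstructured covariance and no T0 covariate.

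Name the adjusted arm difference at T4, in mL/min/kg with its 95% CI, as the single primary contrast, so that no Bonferroni family is needed for it. Keep the baseline-adjusted mixed model for biomarkers with several post-baseline samples.

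The cost is analysis wording only; within-arm change becomes descriptive. The change should be settled before the planned interim analysis at 50% of participant data.

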#### High-intensity interval training (HIIT)

HIIT sessions commence with a two-minute low-intensity warm-up (60%HR_peak_) at 60-70 rpm. Subsequently, six 90-second high-intensity intervals (95%HR_peak_) are performed at high pedaling rates of 80-100 rpm. Intervals are interspersed by 90-second active breaks with unloaded pedaling at 60-70 rpm, aimed to return to 60%HR_peak_. Sessions close with a two-minute low-intensity (60%HR_peak_) cool-down of unloaded pedaling at 60-70 rpm. In total, one HIIT session lasts 21 minutes.

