#### Blood-derived biomarkers

Blood sampling is performed in a fasted state. Samples are obtained from the antecubital vein in supine position. To evaluate the chronic effects of HIIT and MCT on blood-derived biomarkers, resting blood samples are taken between 8:00 and 9:00 AM after ten minutes of supine rest (T_1_, T_4_). To evaluate acute effects on blood-derived biomarkers, blood samples are taken immediately after (T_2_) and two hours after (T_3_) the first HIIT or MCT session. Per sampling time point, two whole blood collection tubes (BD Vacutainer^®^, BD CPT™, 4ml), prefilled with lymphocyte separation medium, and one serum tube (tube vacutainer SSTII serum yel, 6ml) are taken.

Blood samples are analysed regarding the acute and chronic effects of HIIT and MCT on KP modulation, and surrogate markers of neurodegeneration (i.e., sNfL, glial fibrillary acidic protein (GFAP)).

Whole blood samples are centrifuged at 3500 g for 20 minutes, separating peripheral blood mononuclear cells (PBMCs) and plasma. PBMCs are resuspended in plasma, purged into centrifugation tubes, diluted with an equal amount of phosphate-buffered saline, and centrifuged at 2400 g for 10 minutes. The supernatant is discarded. PBMCs are resuspended in cell culture freezing medium, and aliquoted. Aliquots are frozen at -80 °C until analysis. mRNA of PBMCs is isolated using a commercial column-based isolation kit. cDNA synthesis is performed. Based on mRNA and cDNA, gene expression of KP-relevant genes is determined. As such, expression levels of indoleamine 2,3-dioxygenase-1, kynurenine aminotransferase 1–4, kynurenine-3-monooxygenase, aryl hydrocarbon receptor, CYP1A1, interleukin-4-induced-1, and SLC7A5 are determined using real-time quantitative polymerase chain reaction (qPCR), run on a qTower³ G touch (Analytik Jena GmbH, Jena, Germany). Blood serum is centrifuged at 2500 g for 20 minutes, is aliquoted, and frozen at -80 °C until analysis. Targeted metabolomics (liquid chromatography tandem mass spectrometry (LC-MS/MS)) is performed at BEVITAL AS, Bergen, Norway, to determine serum concentrations of tryptophan, KP downstream metabolites (e.g., kynurenine, kynurenic acid, quinolinic acid), and B vitamers. Systemic concentrations of sNfL and GFAP are assessed using a single molecule array (SiMoA HD-1 device, Quanterix, USA) at the University Medical Center of the Johannes Gutenberg University, Mainz, Germany, according to the manufacturer’s instructions.

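### If T2, T3 and T4 biomarkers share one MMRM, the stated terms force one T1 relation on samples taken minutes to three weeks later; a T1 × time term would remove this at almost no cost

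*Protocol article*

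**What the plan says.** All references are to the protocol article.

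- **Model.** The Statistical analysis section has two branches. The first reads "If missing values are < 5%, ANCOVA will be performed to detect time*group interaction effects and main effects of time". Otherwise the plan uses "a baseline-adjusted Mixed Model for Repeated Measures (MMRM) approach", "with group, time and the group × time interaction as fixed effects", with type III sums of squares and a "CS covariance structure over time". No baseline × time term is listed. How baseline enters, as covariate or as response, is not written out.
- **Biomarker sampling.** The Outcomes section states: "Venous blood samples are taken before (T_1_), immediately after (T_2_), and two hours after (T_3_) the first HIIT or MCT session, and at T_4". T1 therefore precedes three later samples.
- **Use of the samples.** The Blood-derived biomarkers section says "Blood samples are analysed regarding the acute and chronic effects of HIIT and MCT on KP modulation". It assigns the resting samples T1 and T4 to the chronic effect and T2 and T3 to the acute effect.
- **Other outcomes.** V̇O2peak and the other non-blood outcomes are assessed "at study entry (baseline, T_0_) and discharge after three weeks (T_4"), so they have one post-baseline time.

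**The concern.** In a baseline-adjusted model without a baseline × time term, one regression slope on T1 serves every later time. For the biomarkers the gaps differ greatly. T1 to T2 spans one session ("In total, one HIIT session lasts 21 minutes"; the MCT session lasts 26 minutes), T3 follows two hours after that session, and T4 comes after three weeks of training and rehabilitation. A sample from the same morning would ordinarily track T1 more closely than one taken three weeks later. Exercise may also change the spread at T2, which changes the slope again.

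If the slopes differ, the common slope is a compromise. It removes too little of a T1 difference between arms from the early contrasts and too much from the late one, and it leaves avoidable residual variance. The biomarkers are not stratification factors, so a chance T1 imbalance is left for the model to handle. Both the acute and the three-week biomarker contrasts are stated secondary aims.

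**Working it through.** The plan gives no biomarker variance or correlation, so there is no figure of its own to reproduce. Its only correlation, 0.6, belongs to the V̇O2peak sample size. Every slope below is therefore an assumption.

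**Inputs.** 61 participants with 15% drop-out: 61 × 0.85 ≈ 52, or 26 per arm. In units of the baseline SD, the standard error of the T1 difference between arms is √(2/26) = 0.277.

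**Formulas** (complete data, compound symmetry). Let r_t be the correlation with T1, s_t the SD at time t, and b_t = r_t·s_t the slope on T1.
- The common slope b̄ is the mean of the three b_t.
- The contrast at time t keeps an error of (b_t − b̄) × (T1 imbalance).
- Residual variance with the common slope is s_t² − 2·b̄·b_t + b̄². With its own slope it is s_t²(1 − r_t²).

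| Assumed slopes T2/T3/T4 | b̄ | b_t − b̄ | Extra variance, formula | Extra variance, simulated (26 per arm) |
|---|---|---|---|---|
| A: 0.90/0.90/0.50 | 0.767 | +0.133/+0.133/−0.267 | 9%/9%/9% | 8.5%/9%/8% |
| B: 1.08/0.90/0.70 (r = 0.90/0.90/0.70, SD 1.2 at T2) | 0.893 | +0.187/+0.007/−0.193 | 13%/0%/7% | 12%/0%/6% |
| C: 0.95/0.95/0.80 | 0.900 | +0.05/+0.05/−0.10 | 3%/3%/3% | 2%/2%/1% |
| Equal: 0.90/0.90/0.90 | 0.900 | 0/0/0 | 0%/0%/0% | −1% to 0% |

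Example, pattern A at T4: 1 − 2(0.767)(0.50) + 0.767² = 0.821, against 1 − 0.50² = 0.75; the ratio is 1.09.

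**Error for a given imbalance, pattern A.** A 1-SE imbalance leaves 0.133 × 0.277 = +0.037 SD at T2 and T3, and −0.267 × 0.277 = −0.074 SD at T4. A 2-SE imbalance leaves −0.15 SD at T4, against a standard error of √(0.75 × 2/26) = 0.24. Type I error conditional on that imbalance is about 9–10%.

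**With missing data, as in the MMRM branch.** Simulation with 30 per arm and 15% missing at T4 gave 0–15% extra variance for the assumed patterns. The T4 over-correction was about −0.09 to −0.37 per unit of T1 imbalance. Time-specific slopes largely removed that dependence. With equal slopes the extra term cost about 1–2% of variance.

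**Wider spread.** Slopes of 0.95/0.80/0.40 give b̄ = 0.717 and simulated extra variance of 59% at T2, 1% at T3 and 9% at T4. This is the extreme of what was tried and lies outside the 0–15% range.

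**Acute and chronic effects modelled separately.** T4 then has its own slope and loses nothing. For T2 and T3 alone, patterns A and C lose nothing because their slopes are equal. In pattern B, b̄ = (1.08 + 0.90)/2 = 0.99. The residual variance is 1.44 − 2(0.99)(1.08) + 0.99² = 0.282 against 0.274 at T2 (3%), and 1 − 2(0.99)(0.90) + 0.99² = 0.198 against 0.190 at T3 (4%).

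**Which branch applies.** If 15% are missing at T4 only, that is 15% of T4 values, 15/3 = 5% of values over T2–T4, and 15/4 = 3.75% over all four samples. The first two lead to the MMRM and the last to ANCOVA. The text does not say how the 5% is counted.

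**The case against.** **A joint model is not stated.** The aims list the acute effect separately, and the sampling text assigns T1 and T4 to one question and T2 and T3 to the other. If the analyses follow that division, the loss all but disappears, as the last variance check shows. This stands, and it is why the point is conditional.

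**The list of terms may be incomplete.** The model is called baseline-adjusted, yet baseline itself is not listed, so the omission of its interaction proves little, and an article may leave such detail to the full plan. Part of this stands: the single slope is an inference. But the text does specify fixed effects, sums of squares and covariance, and a model fitted from those terms has no time-specific slope.

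**Baseline may be a response level.** For outcomes measured only at T0 and T4, a group × time interaction needs T0 as a level of time, and the biomarker model may follow suit. There is then no covariate slope. However, compound symmetry gives T1 the same correlation with every later time, and a contrast of changes from T1 subtracts the T1 difference in full at each time. The relation is still a single one. What stands is that on this reading the fix recasts the model rather than adding a term.

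**Stronger readings.** A reader might infer that the biomarker contrasts are biased, or that precision is certainly lost. The document supports neither. It gives no biomarker correlations, equal slopes cost nothing, and the error exists only given an observed T1 imbalance. The 9–10% conditional type I error needs both a 2-SE imbalance and the widest slope gap among patterns A to C. Nor does the point reach the primary outcome, for which one slope is correct.

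**Conclusion.** The point holds in a limited form. It applies to blood biomarkers, in the MMRM branch, when T2, T3 and T4 are fitted jointly with the stated terms. One T1 relation then covers gaps from under half an hour to three weeks. If the relation weakens with time, which is likely but not quantified in the document, the acute contrasts can be under-corrected and the three-week contrast over-corrected for a chance T1 imbalance. The precision loss is about 0–15% of variance under patterns A to C. It is nil with equal slopes, and larger at T2 only if the slopes spread more widely than in those patterns. Over randomisation the contrasts remain unbiased. This is a free improvement to a secondary analysis and does not threaten the trial's main conclusion.

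**What to change.** For the blood biomarkers, state that T1 enters as a covariate and T2, T3 and T4 are the responses, with fixed effects T1, group, time, group × time and T1 × time. Alternatively, fit a separate T1-adjusted group contrast at each of T2, T3 and T4. Record the choice before the planned interim analysis. Outcomes measured only at T0 and T4 need no change on this account.

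The cost is two extra parameters, and about 1–2% of variance or less if the slopes turn out equal. No new data or participants are needed.
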